## Abstract

**Background:**

Diabetes and hypertension are devastating, deadly, and costly conditions that are very common in seniors. Controlling hypertension in seniors with diabetes dramatically reduces hypertension-related complications. However, blood pressure (BP) must be lowered carefully because seniors are also susceptible to low BP and attendant harms. Achieving “optimal BP control” (ie, avoiding both undertreatment and overtreatment) is the ultimate therapeutic goal in such patients. Regular BP monitoring is required to achieve this goal. BP monitoring at home is cheap, convenient, widely used, and guideline endorsed. However, major barriers prevent proper use. These may be overcome through use of BP telemonitoring—the secure teletransmission of BP readings to a health portal, where BP data are summarized for provider and patient use, with or without protocolized case management.

**Objective:**

To examine the incremental effectiveness, safety, cost-effectiveness, usability, and acceptability of home BP telemonitoring, used with or without protocolized case management, compared with “enhanced usual care” in community-dwelling seniors with diabetes and hypertension.

**Methods:**

A 300-patient, 3-arm, pragmatic randomized controlled trial with blinded outcome ascertainment will be performed in seniors with diabetes and hypertension living independently in seniors’ residences in greater Edmonton. Consenting patients will be randomized to usual care, home BP telemonitoring alone, or home BP telemonitoring plus protocolized pharmacist case management. Usual care subjects will receive a home BP monitor but neither they nor their providers will have access to teletransmitted data. In both telemonitored arms, providers will receive telemonitored BP data summaries. In the case management arm, pharmacist case managers will be responsible for reviewing teletransmitted data and initiating guideline-concordant and protocolized changes in BP management.

**Results:**

Outcomes will be ascertained at 6 and 12 months. Within-study-arm change scores will be calculated and compared between study arms. These include: (1) clinical outcomes: proportion of subjects with a mean 24-hour ambulatory systolic BP in the optimal range (110-129 mmHg in patients 65-79 years and 110-139 mmHg in those ≥80 years: primary outcome); additional ambulatory and home BP outcomes; A1c and lipid profile; medications, cognition, health care use, cardiovascular events, and mortality. (2) Safety outcomes: number of serious episodes of hypotension, syncope, falls, and electrolyte disturbances (requiring third party assistance or medical attention). (3) Humanistic outcomes: quality of life, satisfaction, and medication adherence. (4) Economic outcomes: incremental costs, incremental cost-utility, and cost per mmHg change in BP of telemonitoring ± case management compared with usual care (health payor and societal perspectives). (5) Intervention usability and acceptability to patients and providers.

**Conclusion:**

The potential benefits of telemonitoring remain largely unstudied and unproven in seniors. This trial will comprehensively assess the impact of home BP telemonitoring across a range of outcomes. Results will inform the value of implementing home-based telemonitoring within supportive living residences in Canada.

**Trial Registration:**

Clinicaltrials.gov NCT02721667; https://clinicaltrials.gov/ct2/show/NCT02721667 (Archived by Webcite at http://www.webcitation.org/6i8tB20Mc)

## Introduction

### Impact of Hypertension in Seniors With Diabetes

Diabetes is present in more than 20% of seniors (defined herein as age ≥ 65 years) and often leads to devastating complications and premature death. Hypertension affects over 80% of seniors with diabetes and is widely viewed as the most important cause of cardiovascular complications and death in these patients. Despite its critical importance to health, hypertension remains undertreated and uncontrolled in approximately 40% of seniors with diabetes [1].

Aggressive blood pressure (BP) reduction substantially reduces mortality, cardiovascular events, and microvascular complications in all patients with diabetes [2]. Seniors are at particularly high risk for hypertension-related complications and derive greater treatment benefit than younger patients (ie, greater absolute risk reduction) [3,4]. Achieving BP control in high-risk patients, including those with diabetes, is cost saving (which is rare, as few medical interventions save money over the long term) [5]. Contemporary Canadian guidelines recommend a treatment target BP ≤130 mmHg for these individuals; however, 52% of Canadian seniors with diabetes do not achieve this target [1,6]. Treatment consists of health behavior modification (low sodium diet, optimizing weight, exercise) and antihypertensive drugs [6]. Angiotensin-converting enzyme inhibitors or angiotensin receptor blockers are first-line agents, dihydropyridine calcium channel blockers second line, and thiazide diuretics third line [6,7]. Of note, most patients with diabetes and hypertension will need multiple medications to achieve adequate BP control [8].

### Treatment of Hypertension in Seniors With Diabetes: A Complex Care Challenge

The need for aggressive BP control in seniors with diabetes must be balanced against the very real risk of serious treatment-related complications. Seniors, especially those who have cognitive impairment or who are frail, very old, or institutionalized, are more likely to experience treatment-related complications. These include hypotension, postural dizziness, syncope, falls, and metabolic side effects (including high/low potassium, sodium, and to a lesser extent, elevated glucose levels) [9-12]. Autonomic dysfunction and postural hypotension, more common in older individuals and in those with diabetes, may limit uptitration of antihypertensive drugs even if sitting BP levels are above target [10]. Dose reduction or drug discontinuation may be warranted in many patients to avoid inappropriate polypharmacy, adverse effects (plus additional drug treatments that are used to treat these adverse effects), need for laboratory monitoring, and costs.

Antihypertensive dose reduction or drug discontinuation is clearly warranted when serious adverse effects manifest. However, in asymptomatic patients with low BP, no obvious trigger is present to signal the need for dosage reduction. Furthermore, no widely accepted threshold definition for low BP exists at which dose reduction/discontinuation is mandated. In our opinion, systolic BP (SBP) levels <110 mmHg may confer increased risk for hypotension (and <100 mmHg clearly increase risk) [13].

Importantly, there is no randomized trial evidence that clinical benefits occur from reducing BP to <110 mmHg in seniors with diabetes [9]. For this reason and because it is critically important to avoid drug-related adverse effects (which are quite common [11]), reducing therapy when SBP is below 110 mmHg seems warranted unless a compelling nonhypertension-related indication for an antihypertensive agent is present. The extent to which dosage reductions are made in asymptomatic seniors in real-world clinical practice is unclear. We speculate that dosage adjustments are rarely made either because patients are not monitored frequently (thus, the low BP is not detected) or because a low BP fails to trigger an appropriate dose correction (because providers are primarily trained to focus on high not low readings). This might change if monitoring and a protocol that triggered appropriate dosage modification were implemented.

BP management in seniors with diabetes is further complicated by current guidelines that permit higher SBP treatment targets (<150 mmHg versus the usual <130 mmHg) in patients aged ≥80 years [6,14]. The intent of these guidelines is to allow practitioners to use more lenient targets in seniors who are frail or who, based on clinical opinion, may not tolerate lower BP levels. These guidelines allow us to define an upper limit to the BP therapeutic range for most seniors, above which more aggressive antihypertensive therapy to lower BP should be considered.

### Types of BP Monitoring

To ensure that BP levels are neither too high nor too low, accurate BP monitoring is required. Serial office BP measurements are currently used to monitor the vast majority of Canadians with hypertension. Unfortunately, office readings are inaccurate frequently because recommended measurement techniques are not followed or equipment is not regularly calibrated [15]. Furthermore, in seniors, office measurements are falsely high (white coat effect) in 15%-20% of cases and falsely low (masked effect) in 10%-15% of cases [16]. An additional disadvantage of office measurements is that patients are required to attend clinical appointments, a barrier for seniors who don’t drive or who have mobility or financial limitations. Office measurements, therefore, may be infrequent, and this limits the ability to make timely therapeutic adjustments to address low or high BP.

Because of these limitations of office BP monitoring, contemporary guidelines strongly endorse use of out-of-office measurement [6]. Out-of-office measurement has additional advantage over office BP in that it allows multiple temporally separated readings to be performed. This provides a more accurate assessment of true BP because BP is a continuous parameter that changes every second of the day. Out-of-office measurement is currently performed by measuring 24-hour ambulatory BP monitoring (ABPM) or home BP monitoring. ABPM is widely regarded as the gold-standard measurement method [6,17], but is not widely available, not widely reimbursed, and often not well tolerated (because frequent measurements are needed and sleep disturbance may occur). Home BP measurement is thus much more commonly used for follow-up BP measurement [6]. Nearly 50% of hypertensive Canadians own a home monitor [18]. Home measurement has additional advantages, it increases treatment adherence and patient activation (by encouraging BP self-monitoring) [19-21], and when used alone, modestly reduces SBP (by 1.3 mmHg [95% CI 0.3-2.2] in a meta-analysis of 17 studies) [22].

### Methods of Performing Home BP Measurement

Measuring a home BP series is the recommended method of performing home BP measurement [6]. A home BP series is composed of duplicate readings in the morning and evening (ie, 4 per day) daily for 7 days [6]. Readings taken on the first day are discarded and the latter 6 days (24 measurements) are averaged. If BP levels are at target, the home BP series is repeated quarterly. If BP levels are uncontrolled, therapeutic adjustments are made and the home BP series repeated in 4 weeks.

Home readings can be used in 1 of 3 major ways: (1) by the patient alone (who bears responsibility for giving the readings to their provider); (2) via telemonitoring, in which readings are automatically summarized and sent to the care provider; and (3) through telemonitoring plus protocolized case management, in which the summarized readings are reviewed by a case manager authorized to adjust treatments. BP telemonitoring ± case management is not being used in Canada because data on effectiveness and feasibility in this country are limited, the required technological infrastructure is not available, and a provider reimbursement plan does not exist.

Although contemporary guidelines strongly endorse home BP measurement, describe how to self-measure BP and outline how to perform a home BP series, more needs to be done to ensure correct uptake in clinical practice [6]. A major drawback is the onus is placed on the patient to measure, record, and present the home readings to their care provider though, this patient alone method has the advantage of requiring no additional resources and is the predominant method used in Canada. However, patients often forget to record their measurements, do not follow the recommended protocol (timing, frequency, and number of measurements), and/or self-select readings for presentation to their physician [23,24]. Recent data indicate that less than one-third of patients report ≥80% of measurements to their physician [25]. Important physician-related barriers to proper use of home BP measurement also exist. Physicians often do not calculate the mean BP (treatment adjustments are based on the mean), do not scan and upload hand-written BPs into their Electronic Medical Record (thus, no permanent record is available), and/or do not act on out-of-target readings (“therapeutic inertia”) [23,24].

Home BP telemonitoring is a second method that, through process automation and protocols, can potentially overcome some of the aforementioned barriers [25,26]. BP telemonitoring consists of electronically and securely transmitting remotely collected BP measurements in real time to a central electronic health care portal. Data can be summarized for use by patients and providers, this includes calculation of BP means and graphing temporal trends in BP. Mean BPs that are too high or low can be flagged for action, whereas those in the normal range provide evidence for optimal control. Telemonitoring may eliminate the need for in-person clinic visits, and contributes to health care delivery efficiency and making better use of provider time. A recent meta-analysis of 23 randomized controlled trial (RCTs; 7037 patients) reported that home BP telemonitoring reduced BP by 5/3 mmHg compared with usual care (*P*<.0001 for both SBP and diastolic BP) [27]. This is a clinically important reduction, a 5-mmHg reduction in BP in high-risk patients (including diabetes) reduces cardiovascular events by 15% [28] and, in patients with diabetes, reduces stroke by 13% [29].

The third method of implementing home BP monitoring is to combine telemonitoring with case management. Case managers, usually nurses or pharmacists, work collaboratively with patients and physicians to optimize health behaviors, monitor risk factors, implement therapeutic adjustments, encourage adherence, and coordinate follow-up care [30-32]. Case management is well established and is currently used in contemporary clinical practice (our Pharmacare industry partner specializes in providing pharmacist case management services to seniors living in apartments, lodges, and assisted living facilities). Case management works best when the case managers have prescribing authority and use algorithms or protocols to make guideline-concordant therapeutic initiations and adjustments [30,33,34]. This can potentially overcome therapeutic inertia. BP improvements are greater when interventions have combined case management with telemonitoring [27]. Thus, it is essential to study case management because it may be needed in conjunction with telemonitoring to maximize the effectiveness of the latter.

### Reasons Why Home BP Telemonitoring is not Currently Used in Canada

Collaboration between health care providers, decision makers, and device makers/technology companies is limited. This collaboration is required to make telemonitoring feasible. Historically, such collaborations have been rare, primarily because of lack of dialogue and interaction among potential partners.

Canadian data are very limited. A 1-year study in 110 hypertensive patients with diabetes (age ≥30 years; mean age 63 years) home BP telemonitoring and automated cellphone text messages that instructed patients to seek follow-up care was compared with usual care [35]. BP was reduced by 7.1/2.3 mmHg (*P*<.005) in the telemonitoring arm, and there was a 20% increase in the proportion of patients with controlled BP (51% versus 31%; *P*<.05). To our knowledge, this is the only published Canadian study of relevance. Patients did not receive treatment recommendations, seniors were not specifically studied, cost-effectiveness was not assessed, usability or acceptability not reported, and case management was not used. For these reasons, another trial is warranted to build on this important foundational work.

Costs have, historically, been a major barrier. This is primarily because of uncertainty over who will pay for teletransmission, health portal development, and portal maintenance. However, home BP monitors are now inexpensive and widely used, cellphone or Internet use is very high (enabling convenient, secure electronic data transmission), payment solely for teletransmission is not necessary (ie, as long as an existing data plan is present, the extra data usage for intermittent BP teletransmission is minimal), and established companies exist that specialize in health data transmission and health portal creation and maintenance. Thus, because of these technological advancements, fewer barriers remain. Importantly, BP control in high-risk populations (including diabetes) is cost saving [5]; therefore, health care payors funding or subsidizing this expenditure can expect initial costs to be offset by substantial downstream savings. In the United States, health care payors can spend an additional $600-1250 USD per patient per year controlling BP in high-risk patients yet still remain cost-neutral, this is a huge “safety margin” that supports the potential for telemonitoring to be cost-effective (because total costs are likely to be under these thresholds). Because previous studies have demonstrated mixed results in terms of BP telemonitoring cost-effectiveness [27,36], it is important to create a system that minimizes costs, maximizes cost-effectiveness, and leverages expenditures already borne by the individual for other reasons (ie, mobile phones, set top boxes, and data plans) to promote health care system sustainability.

Need for user training had been nearly prohibitive. This has largely been eliminated through technological advancements and major advances in user-friendliness. Systems require little additional action (other than BP self-measurement) because BP teletransmission can be automated once the reading is taken.

### Summary of Rationale for a Tech-Based Canadian Study in High-Risk Seniors

To summarize, hypertension is very common in seniors with diabetes and substantially increases morbidity, mortality, and health costs. Controlling BP markedly reduces complications and can be cost saving. However, BP reduction is not the only goal, in some cases (white coat effect, low BP), drug dosage reductions are appropriate. BP management in seniors with diabetes is complicated by the need to balance cardiovascular risk reduction against the risk of adverse effects and polypharmacy. Age-appropriate BP thresholds and targets in the very elderly (age ≥ 80 years) must also be considered. Effective BP management is further hindered by the near ubiquitous dependence on inconvenient, infrequently performed and inaccurate office BPs to titrate therapy. Home BP readings should be used instead, but the optimal implementation method in terms of effectiveness, acceptability, and costs remains unclear. Measuring and reporting home BP could be left up to the patient, automated using telemonitoring, or automated and protocolized using telemonitoring and case management.

Although over 20 published trials reported clinically important BP reductions using home BP telemonitoring and case management, data in seniors are lacking, and it is important to confirm feasibility, effectiveness, safety, usability, and acceptability in this population in Canada. Importantly, prior studies have focused on reducing high BP only; in seniors, avoiding low BP and polypharmacy are equally important. Telemonitoring has initial (BP device) and ongoing (teletransmission and health portal maintenance) costs. Case management costs must also be considered. These costs ought to be offset by cost reductions achieved through avoidance of hypertension-related complications, drug-related adverse events, and reduced drug use. If done the way we propose, telemonitoring has the potential to be highly cost effective in these high-risk patients. However, a formal economic analysis is needed before widespread implementation can be justified.

### Objectives

This Telemonitoring and Protocolized Case Management for Hypertensive Community-Dwelling Seniors With Diabetes (TECHNOMED) trial is designed to (1) assess the “real world” effectiveness and safety of home BP telemonitoring alone or in combination with protocolized pharmacist case management in seniors with diabetes and hypertension when compared with “enhanced” usual care; (2) evaluate the usability and acceptability of home BP telemonitoring; and (3) examine the cost-effectiveness of home BP telemonitoring alone and home BP telemonitoring plus protocolized case management.

In aggregate, these objectives will assess the impact on a comprehensive range of outcomes important to patients, providers, decision makers, industry partners, and funders.

## Methods

### Study Design

In this 1-year pragmatic, prospective randomized open label trial with blinded ascertainment of end points, 300 patients will be randomly assigned (1:1:1) to one of 3 study arms (Figure 1): (1) enhanced usual care (in which participants will be given a home monitor but BP teletransmission will not be accessible and case management not available to them); (2) home BP telemonitoring alone; and (3) home BP telemonitoring plus protocolized case management.

**Figure 1 figure1:**
[figure not shown]
Study design.

### Randomization

Computer-generated randomization will be performed centrally and independently by the EPICORE center (www.epicore.ualberta.ca) to ensure allocation concealment from all research personnel. Randomization will be stratified by baseline SBP (<140 mmHg versus ≥140 mmHg). Although clinic staff and pharmacist case managers cannot be blinded to allocation status, all outcome assessments will be performed by research assistants working independently from regular clinic staff and the pharmacist case managers.

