### Analytic Plan for Major Outcomes

#### Aim 1: Effectiveness of Telemonitoring ± Protocolized Case Management

All primary analyses will be conducted according to the intention-to-treat principle. The primary outcome is the 1-year change in proportion of patients with overall 24-hour SBP in the optimal range (SBP is used because it is a stronger predictor of risk and because diastolic BP is rarely elevated in seniors [10]). We will use 24-hour ABPM because it is the gold-standard measurement method and the best validated clinical trial BP end point [40]. The 24-hr ABPM therapeutic range will be 110-129 mmHg in patients aged 65-79 years and 110-139 mmHg in those ≥ 80 years. Justification for the upper thresholds chosen is based on current guidelines that specify an overall 24-hour ABPM of ≥130 mmHg as high in all patients, including those with diabetes [6]. In patients ≥80 years, we will allow the option of a higher 24-hour target of <140 mmHg (ambulatory BP threshold definitions of normal versus high are lower than office BP thresholds; therefore, this threshold is analogous to the Canadian guideline concordant <150 mmHg office BP target that is allowed in older frailer patients [6]).

Major secondary outcomes will include the change in mean 24-hour SBP and diastolic BP (overall, daytime, and nighttime). Home BP and the automated BP measurements taken at each study visit will be examined similarly. Additional major outcomes will include postural BP changes and changes in A1c, lipids, anthropomorphic indices, quality of life, depression/anxiety, satisfaction with medical care, resource utilization, and the safety end points described previously.

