##### Data Analysis

First, variables will be examined descriptively and graphically, including assessments of temporal trends and tests of normality. Second, the 6-month and 1-year mean change from baseline in each outcome will be calculated and compared between study arms (each intervention arm to the control arm, then between intervention arms) using chi-square tests for dichotomous outcomes and unpaired *t*-tests for continuous outcomes. Third, multivariable predictors of the 1-year change in a given outcome will be identified using appropriately constructed and calibrated logistic regression models for dichotomous outcomes (including the primary outcome) or linear regression models for continuous ones. Initial models will adjust for age, sex, SBP, and residential site (eg, Greater Edmonton Foundation versus Rosedale). Examples of additional covariates that may be examined include sociodemographic variables, comorbidities, baseline medications, primary care physician, and tests of potential interaction.

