##### Sample Size Considerations

The study will be adequately powered to detect a clinically important 20% absolute difference in the primary outcome between each intervention arm and usual care and similar 20% difference between the 2 intervention arms (20% has been previously identified by a consensus of Canadian experts as the required minimum clinically important difference for any new hypertension [or any other cardiometabolic] intervention directed at patients with diabetes [53]). Based on pilot data collected in 60 seniors residing in supportive living at two Edmonton sites, only 18% were within the therapeutic range at baseline. Assuming 5% improvement with usual care (related to secular or temporal trends and trial participation or Hawthorne type effects), 20% further improvement with telemonitoring, and a further 20% improvement with telemonitoring + case management, a 2-tailed alpha of 0.05, power of 0.80, the required sample size will be ~80 patients per arm or 240 total. Accounting for ≈20% attrition over 1 year, 100 patients per arm or 300 patients total will be recruited.

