### Subgroup Analyses and Substudies

Analyses of interest include examination of the effect of telemonitoring in subjects aged 80 years or greater as well as substudies on vascular stiffness, orthostatic changes, and novel BP measurement methods. In addition, passive, long-term follow-up using linked administrative data are planned to ascertain effects on cardiovascular morbidity and mortality.

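### The primary endpoint's upper limit steps up at age 80, but the stated arm comparison is an unadjusted chi-square: some precision is lost, though there is no bias

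*Protocol article*

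**What the plan says.** All places are in the protocol article.

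- **Aim 1** defines the endpoint: "The primary outcome is the 1-year change in proportion of patients with overall 24-hour SBP in the optimal range". The range depends on age: "The 24-hr ABPM therapeutic range will be 110-129 mmHg in patients aged 65-79 years and 110-139 mmHg in those ≥ 80 years".
- **Randomization** names one stratification factor: "Randomization will be stratified by baseline SBP (<140 mmHg versus ≥140 mmHg").
- **Data Analysis** compares each intervention arm with control, and then the two intervention arms, "using chi-square tests for dichotomous outcomes". A third step looks for multivariable predictors of the 1-year change, using logistic models that expressly include the primary outcome: "Initial models will adjust for age, sex, SBP, and residential site".
- **Subgroup Analyses and Substudies** names one subgroup: "examination of the effect of telemonitoring in subjects aged 80 years or greater". The other items there are substudies or long-term follow-up.
- **Sample Size Considerations** gives the rates: "only 18% were within the therapeutic range at baseline", then "Assuming 5% improvement with usual care", and a further 20 points for each step up in intervention.

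**The concern.** Two patients with the same 24-hour systolic pressure of 135 mmHg are scored differently if one is 79 and the other 80. The younger is out of range and the older is in range. Age group is thus tied to success by the endpoint's own definition, not merely through prognosis. The chi-square test ignores it, and randomisation leaves it to chance. An arm that happens to hold more patients aged 80 or over will show more successes with no difference in blood pressure. At stake is some avoidable noise in a contrast sized for a 20-point difference, in a design with little power to spare. A lesser matter is uneven numbers across arms in the only named subgroup.

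**Working it through.** **Inputs from the protocol article.** Upper limit 129 mmHg below age 80 and 139 mmHg from 80. 18% in range at baseline. One-year rates of 18 + 5 = 23%, 23 + 20 = 43% and 43 + 20 = 63%. About 80 evaluable per arm (100 × 0.8).

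**Inputs assumed, because the documents do not give them.** Share aged ≥80, q = 0.3 to 0.6. 24-hour systolic pressure normal with SD 10 to 18 mmHg. Mean in the older group 0 or 5 mmHg higher.

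**Step 1. Power on the plan's own rates.** With n = 80 per arm and two-sided alpha 0.05, the pooled normal formula gives 77.3% for 23% vs 43% and 72.1% for 43% vs 63%. These are the base for judging a precision loss. Whether 80 per arm follows from these rates is a separate matter.

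**Step 2. Gap in the share in range between age groups.** For each q and SD, the mean is chosen so that 18% overall are in range, and the gap d is the in-range share at ≥80 minus that at <80.

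| q | SD | Older group higher by | In range <80 | In range ≥80 | Gap d |
|---|---|---|---|---|---|
| 0.3 | 10 | 0 | 9.5% | 37.8% | 28.4 |
| 0.5 | 15 | 0 | 9.5% | 26.5% | 16.9 |
| 0.5 | 15 | 5 | 13.3% | 22.7% | 9.3 |
| 0.6 | 18 | 5 | 13.1% | 21.2% | 8.1 |

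(Gaps are from unrounded shares.) Over the whole grid the gap is about 14 to 28 points with equal pressures and 8 to 14 points with 5 mmHg higher pressure at ≥80.

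**Step 3. Chance imbalance in the share aged ≥80 between two arms.** SD = sqrt(2q(1−q)/n).

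- q = 0.3: sqrt(2 × 0.3 × 0.7/80) = 7.25 points; 95% limits ±14.2.
- q = 0.5: sqrt(2 × 0.5 × 0.5/80) = 7.9 points; 95% limits ±15.5.
- q = 0.6: sqrt(2 × 0.6 × 0.4/80) = 7.75 points; 95% limits ±15.2.

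**Step 4. Resulting shift of the unadjusted contrast.** Shift = imbalance × d.

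- Largest: 14.2 × 0.284 = ±4.0 points.
- Middle (q = 0.5, SD 15): 15.5 × 0.169 = ±2.6, or 15.5 × 0.093 = ±1.4.
- Smallest: 15.2 × 0.081 = ±1.2 points.

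For scale, the standard error of the contrast at 23% vs 43% is sqrt(0.23 × 0.77/80 + 0.43 × 0.57/80) = 7.3 points, or ±14.2 at 95%. The age component is already inside that figure. As a share of variance it is between (1.2/14.2)² = 0.7% and (4.0/14.2)² = 8%.

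**Step 5. Power by simulation** (40,000 runs, 80 per arm, q = 0.5, outcome taken as 12-month status). The adjusted test is an age-stratified Mantel-Haenszel test.

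| Contrast | Gap d | Chi-square | Chi-square, age-stratified randomisation | Adjusted | Adjusted, age-stratified randomisation |
|---|---|---|---|---|---|
| 23 vs 43% | 10 | 78.2% | 78.1% | 78.1% | 78.3% |
| 23 vs 43% | 20 | 77.9% | 78.5% | 79.3% | 79.5% |
| 23 vs 43% | 30 | 77.8% | 79.3% | 81.5% | 82.2% |
| 43 vs 63% | 10 | 71.2% | 71.5% | 71.9% | 71.7% |
| 43 vs 63% | 20 | 71.3% | 71.9% | 73.6% | 73.4% |
| 43 vs 63% | 30 | 71.6% | 72.9% | 76.2% | 77.0% |

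The simulation error of each figure is about sqrt(0.78 × 0.22/40000) = 0.2 points.

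**Step 6. Type I error** (33% in both arms). Without age-stratified randomisation it is 5.0-5.2% for the chi-square and 4.9-5.1% for the adjusted test. With age-stratified randomisation but an unadjusted chi-square, it falls to 4.5% at d = 20 and 4.0% at d = 30. Stratifying without adjusting makes the test conservative and does not use the balance gained.

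**The case against.** A reader might infer that randomisation is flawed, or that chance age imbalance biases the primary result. The documents do not support this. Allocation is random, the imbalance is equally likely to favour either arm, and the test's error rate already allows for it (Step 6). Choosing stratification factors is a legitimate design decision.

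A reader might also infer that age will enter the model as a straight line and miss the step at 80. Data Analysis says only age, within suitably constructed models. The coding is a detail that the analysis plan may settle, and it is not counted as a fault here.

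The strongest objection is that adjustment for age is already planned and covers the primary outcome. That stands in large part: adjustment recovers nearly all the precision that stratification could, so the randomisation scheme is the lesser issue. What remains is that the model is introduced as a search for predictors, after the between-arm chi-square, and the article does not say which of the two is decisive.

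Two further objections also stand. The size depends on assumptions, and higher pressure in the older group shrinks it. The endpoint is also worded as a change in proportion, with no different age rule stated for baseline. If it is analysed that way with the same window at both times, part of the age offset cancels.

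Uneven numbers in the subgroup aged 80 or over cost it a little precision but do not invalidate it.

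**Conclusion.** The point holds as a modest loss of efficiency. The endpoint is defined by age group, and the stated arm comparison ignores it. Under the assumptions listed, the gap in the share in range is about 8-28 points, and chance age imbalance moves the unadjusted contrast by about ±1 to ±4 points (95% limits) on a 20-point target. The gap is calibrated to the 18% baseline rate. A 30-point gap at 12 months with half the patients aged 80 or over would give ±4.7. Analysis of change from baseline would give less.

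Adjusting for the age group gains almost nothing at a 10-point gap (−0.1 and +0.7 points of power in the two contrasts), about 1-2 points at 20, and about 4-5 points at 30. Adding age to the randomisation strata on top of that gains under 1 point.

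**What to change.** State that the decisive primary comparison is the covariate-adjusted analysis already foreseen in Data Analysis. Enter age as <80 versus ≥80, matching the endpoint definition, together with the blood pressure stratum used at randomisation. Report the effect as a standardised risk difference, so that it stays on the scale of the 20-point target, and keep the chi-square as supportive. Both covariates are already collected, so the cost is one model term and a sentence in the plan.

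Optionally, if randomisation has not begun, add age group as a second stratification factor. That makes four strata in a central computer-generated scheme for 300 patients, which is a small set-up change. Its main benefit is balance across arms in the subgroup aged 80 or over. It should not be adopted without the adjusted analysis, for the reason shown in Step 6. If randomisation has begun, the analysis change alone is sufficient.
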